### Sample size

In order to provide a power of 90% to detect an effect size (Cohen’s d) of at least 0.5 servings/day, 172 participants (86 in the intervention group and 86 in the control group) are required. Based in the dropout of similar studies [28–30], the final sample size is increased by 20% to reach 206 children (8 classrooms with a minimum of 26 children per class).

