#### Secondary outcomes: Qualitative outcomes

Determinants of eating behavior: evolution of determinants proposed (attitude, subjective norms and perceived behavioral control) will be analyzed by a questionnaire designed according to bibliographic proposals [34]. Each determinant will be measured by a minimum of 3 items that will be answered by children marking a number on a 1–5 scale from “totally disagree” to “totally agree”. Validity of the survey will be checked by its internal consistency (Cronbach’s alpha).
Social demographic outcomes and families’ FV consumption habits: data will be collected by a questionnaire designed by the Department of Sociology 2 of the University of the Basque Country to obtain the following information:
Parental educational attainmentParental employment situationTheir perceived importance of their children’s FV intakeTheir level of knowledge concerning FV recommended intakeFV availability and accessibility at homeWhere children have their main mealChildren’s TV watching habits during mealsParents’ FV consumption habits.

Codified surveys will be sent by means of the children inside codified sealed envelopes. These will be filled out at home by parents and returned to school. Questionnaires of behavior determinants of behavior will be completed in 20 min by children at school under the supervision of a nutritionist. All the questionnaires will be completed at the three times described previously (T0, T1, T2) during the academic year and one year after intervention will be finished (T3).

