### Statistical analysis

Descriptive statistics will be carried out to describe baseline characteristics of intervention and control group to assure comparability between groups.

Intra-group and inter-group FV intake differences at T0, T1, T2 and T3, will be analyzed by Student’s *t* test or non-parametric tests (Wilcoxon signed-rank test and Mann–Whitney U test). The same tests will be carried out to study the evolution of determinants of eating behavior (attitude, subjective norms, perceived behavioral control and intention) at different times.

To understand the relationship between determinants of behavior and behavior itself (FV consumption), multiple linear regression and structural equation modeling (SEM) analysis will be done at different times. Covariance of classic relationship of TPB determinants will be proposed. It will allow us to check the validity of the proposed model, as well as the influence of each determinant on the others and its significance. Changing models will be made by using difference on TPB determinants between different times.

Model validity will be established by comparative fit index (CFI), root mean square-error of approximation (RMSEA) and chi square/degrees of freedom (χ2/df). A good model will be determined by high values of CFI (> 0.90), low values of RMSEA (< 0.10) and χ2/df values from 1 to 3 [35, 36].

Multiple linear regression will be used to study the effect of social demographic variables in the effectiveness of the intervention.

Statistical analyses will be made using STATA 14.0, IBM-SPSS 24.0 and AMOS 24.0 statistical software. IC of 95% and significance level of *p* < 0.05 will be assumed.

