## Discussion

An increase in the consumption of FV at the end of the program may indicate that the proposed program is a valid and useful tool for achieving changes in their consumption. A negative result will be helpful in redefining new strategies in the framework of changing habits in the consumption of FV. In addition, the one-year analysis (T3) would indicate the adherence to the program through time.

Thanks to SEM analysis, we will be able to measure the influence of different determinants on the process of change in the habit of eating FV, an important and new advance for future designs of more focused programs.

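### The SEM fit rule puts a floor of 1 on χ2/df, so read literally it classes models with RMSEA = 0 and CFI = 1 as not good

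*Protocol article*

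**What the plan says.** The Statistical analysis section names three indices as the basis for judging the SEM: "Model validity will be established by comparative fit index (CFI), root mean square-error of approximation (RMSEA) and chi square/degrees of freedom". It then gives the cut-offs. The first is "A good model will be determined by high values of CFI (> 0.90", and the sentence continues with "low values of RMSEA (< 0.10) and χ2/df values from 1 to 3". CFI and RMSEA are therefore limited on one side only, while χ2/df has both a floor and a ceiling. Two references are cited for the cut-offs. Nothing in the article explains the floor or says that a ratio below 1 is acceptable.

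The rule can apply more than once, because "multiple linear regression and structural equation modeling (SEM) analysis will be done at different times", and models of change between time points are planned as well. The model's degrees of freedom and the estimator are not given. On measurement, the Secondary outcomes section says "Each determinant will be measured by a minimum of 3 items", answered on a 1–5 scale.

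**The concern.** χ2/df measures misfit, and smaller is better. When the model is correct, the fit statistic has an expected value of about df, so the ratio scatters around 1 and values below 1 are ordinary. A floor of 1 treats that ordinary lower half as a defect.

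The floor also works against the other two criteria. RMSEA and CFI reach their best possible values exactly when χ2/df is 1 or less. A model with a ratio below 1 is therefore as good as can be on two of the three indices and fails the third.

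At stake is the verdict on whether the Theory of Planned Behavior model is valid, which feeds the secondary objective on how the determinants relate to intake.

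**Working it through.** **Inputs.** From Statistical analysis: CFI > 0.90, RMSEA < 0.10, χ2/df from 1 to 3. From Sample size: N = 172 evaluable and 206 recruited. N serves here only to scale RMSEA and to set the simulation size. Model df is not stated, so a range of 1 to 200 is assumed.

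**The plan's own figure.** The SEM rule carries no computed figure. The N used here does reproduce. For "power of 90% to detect an effect size (Cohen’s d) of at least 0.5 servings/day", taking d = 0.5 and a two-sided 5% level (two-sidedness is assumed), 86 per group gives 90.3% power, hence 172; and 172 × 1.2 = 206.4, i.e. 206.

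**Step 1: how the three indices relate.** Let T be the model chi-square.
- RMSEA = √[max(0, (T/df − 1)/(N − 1))]. If T/df ≤ 1, RMSEA = 0.
- CFI = 1 − max(0, T − df)/(misfit of the baseline model). If T ≤ df, the numerator is 0 and CFI = 1.

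Every model with T/df < 1 thus has RMSEA = 0 and CFI = 1. This follows from the formulas and does not depend on df, N or the distribution of the items.

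**Step 2: what the ceiling of 3 adds.**
- χ2/df = 3 corresponds to RMSEA = √(2/171) = 0.108 at N = 172 and √(2/205) = 0.099 at N = 206.
- RMSEA = 0.10 at N = 172 corresponds to χ2/df = 1 + 0.01 × 171 = 2.71.

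The ceiling nearly duplicates the RMSEA limit. The floor is the main thing that the χ2/df criterion adds.

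**Step 3: how often a correct model falls below 1.** Asymptotically T follows a chi-square distribution with df degrees of freedom. The rule fails a correct model with probability P(T < df) + P(T > 3df).

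| df | below 1 | above 3 | fails 1-to-3 rule |
|---|---|---|---|
| 1 | 68.3% | 8.3% | 76.6% |
| 2 | 63.2% | 5.0% | 68.2% |
| 5 | 58.4% | 1.0% | 59.4% |
| 10 | 56.0% | 0.1% | 56.0% |
| 48 | 52.7% | 0.0% | 52.7% |
| 200 | 51.3% | 0.0% | 51.3% |

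The second column stays above one half because the median of a chi-square lies below its mean. The fourth column becomes the third if the floor is dropped.

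**Step 4: does this carry over to N = 172?** Correct models were simulated under assumed structures.
- Observed-score path model, df 2: 62.7% below 1 and 5.1% above 3, so 67.8% fail.
- Four factors with three items each, df 48, normal data: 49.2% fail (mean ratio 1.03; Monte Carlo error about 2 points).
- The same df-48 model with skewed five-point items, fitted by normal-theory maximum likelihood: 23% fail (mean ratio 1.17).

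Scaling T upward by a constant shows the same pattern. With 20% inflation the failure rate is 64.7% at df 2 but 21.3% at df 48. Classroom clustering would push T in the same direction.

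**The case against.** The best defence is that 1 to 3 is a customary rule of thumb, given with references that cannot be consulted here, and that no analyst who sees RMSEA = 0 and CFI = 1 would call the fit poor. The floor might even be deliberate, as a warning of overfitting. This is plausible, but it does not rescue the wording: the article presents the range as part of what determines a good model and gives no such reason for the floor.

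Several stronger readings are tempting and should be resisted.
- *A correct model would fail more than half the time in this trial.* That holds under the asymptotic reference distribution. At N = 172 the simulated rate ran from about 68% down to 23%, depending on df and item distribution, and the article fixes neither.
- *The criteria contradict one another.* They can all be met: at N = 172 any model with CFI above 0.90 and a ratio from 1 up to just under 2.71 passes. The conflict is confined to models below 1.
- *Well-fitting models will be discarded, or altered until they fit worse.* The article does not say what happens to a model outside the range.
- *The objective on determinants and intake depends on this rule.* Multiple linear regression is planned for the same question and does not use it.
- *The Discussion raises the stakes.* Its statement "Thanks to SEM analysis, we will be able to measure the influence of different determinants" describes a purpose and contains no fit threshold.

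**Conclusion.** The rule is wrong as written, and the consequence is small. That a ratio below 1 goes with RMSEA = 0 and CFI = 1 needs no distributional assumption, so the misclassification is certain for any such model if the rule is applied literally.

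How often a correct model would be caught is uncertain. It is 51% to 68% for df from 200 to 1 if T follows its asymptotic chi-square distribution. It stays near two thirds for a small path model at N = 172, and can drop to about a quarter for a larger latent model when skewed items inflate the statistic. A floor that bites less often only because the statistic is biased upward is not thereby justified.

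The effect is limited to the secondary SEM analyses. The primary intake comparison, the tests on the determinants and the regressions are untouched.

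**What to change.** In Statistical analysis, replace the range for χ2/df by *χ2/df of at most 3*, with no lower bound. If the floor was meant as a warning of overfitting, state that in a separate sentence and keep it out of the fit criteria.

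With the floor removed, the χ2/df criterion fails a correct model in 8.3% of cases at df 1, 5.0% at df 2, 1.0% at df 5, 0.1% at df 10 and almost never from df 20 (asymptotic figures). Applied together with RMSEA < 0.10 at N = 172, the corresponding figures are 10.0%, 6.7%, 1.9%, 0.3% and about 0%.

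The cost is one line of wording, with no change to data, design or any other analysis.

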## Discussion

An increase in the consumption of FV at the end of the program may indicate that the proposed program is a valid and useful tool for achieving changes in their consumption. A negative result will be helpful in redefining new strategies in the framework of changing habits in the consumption of FV. In addition, the one-year analysis (T3) would indicate the adherence to the program through time.

Thanks to SEM analysis, we will be able to measure the influence of different determinants on the process of change in the habit of eating FV, an important and new advance for future designs of more focused programs.

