**Trial Registration:**

This study has been retrospectively registered at ClinicalTrials.gov. Identifier: NCT03400891. Data registered: 17/01/2018.

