## Methods

### Design

A cluster randomized controlled trial will be carried out over an academic year at school level. Classrooms from different schools and schools themselves will be the clusters of the study. Clustering was chosen because this is the easiest way to implement an intervention program at school level. In this way the phenomenon of contamination between children from the same classrooms is avoided.

Whole classes (a minimum of 26 children per classroom) from different schools will be part of the intervention or control group. The control group allows us to analyze the direct effect of the intervention and to discard an increase of FV intake by seasonality (first measurements will be in October and final ones in June) or other factors. The study was approved by the Ethic Committee of the University of the Basque Country (CEISH/262/2014/[name]) and all parents or legal guardians and school directors and teachers will be sent an informed consent before the study starts. Written informed consents will be sent to parents or legal guardians through the children. After having received consents, the collection of the first data will be carried out followed by the randomized allocation of classrooms.

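### No single between-arm contrast is named as the test of effectiveness, and the Discussion reads success from an increase with no comparator, so a seasonal within-arm rise could be taken as an effect.

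*Protocol article*

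**What the plan says.** - **Protocol article, Discussion:** the sentence that opens "An increase in the consumption of FV at the end of the program may indicate that the proposed program is a valid" names no comparator. The same paragraph treats the one-year visit separately: "the one-year analysis (T3) would indicate the adherence to the program through time".
- **Statistical analysis:** the tests are listed without ranking, in a sentence that opens "Intra-group and inter-group FV intake differences at T0, T1, T2 and T3, will be analyzed by"; the methods are t tests or rank-based alternatives. One threshold covers everything: "significance level of *p* < 0.05 will be assumed". No visit or contrast is marked as deciding, and the between-arm tests named adjust for neither baseline intake nor classroom.
- **Design:** the control group is meant to let the programme's own effect be seen. Its other stated purpose is "to discard an increase of FV intake by seasonality (first measurements will be in October and final ones in June) or other factors".
- **Sample size:** 90% power for an effect of 0.5, with 86 children per arm (172 in total), raised by 20% to 206.
- **Study procedure:** T0 is in September (the Design section says October), T1 in January during the programme, T2 in June after it, and T3 in June one year later.
- **Objectives:** the main objective is effectiveness of the programme. The first secondary objective is the change in FV intake in the study population after the intervention.

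**The concern.** The Design section recognises that intake may rise between autumn and June whatever the programme does, and gives the control group the job of removing that rise. The Discussion then describes a supportive result in words that a purely seasonal rise would satisfy. The Statistical analysis section supplies a test that would pick up such a rise, the within-arm comparison, and lists it beside the between-arm comparison without saying which one answers the main objective.

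A within-arm change estimates the programme effect plus season, ageing, and any effect of repeated recording. Only the between-arm difference isolates the programme. If the results paper followed the Discussion wording literally, a significant September-to-June rise in the intervention arm could be reported as effectiveness. Leaving the visit unnamed also leaves room to choose among T1, T2 and T3 afterwards.

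**Working it through.** **1. What the sample size assumes.** Inputs from the Sample size section: d = 0.5, power 90%, 1:1 allocation. The effect is called Cohen's d but given in servings/day, so SD = 1 is implied. Two-sided 0.05 is assumed, because sidedness is not stated.

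Normal approximation: n per arm = 2 × (1.960 + 1.282)² / 0.5² = 84.06, so 85. The t-based solution is 85.03, rounded up to 86. This matches the stated 86. A one-sided test would need only about 69 per arm and does not match. The dropout step also matches: 172 × 1.2 = 206.4. The trial is therefore sized for one two-sided between-arm comparison.

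**2. Season and the within-arm test.** Assumptions, none of them in the article: no programme effect, a rise of δ SD by June shared by both arms, correlation r between T0 and T2, 86 children in the arm, two-sided 0.05, no clustering.

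SD of change = √(2(1 − r)); noncentrality = δ√86 / √(2(1 − r)). The chance of significance comes from the noncentral t distribution with 85 df.

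| r | SD of change | δ = 0.2: noncentrality, chance | δ = 0.3: noncentrality, chance |
|---|---|---|---|
| 0.3 | 1.183 | 1.57, 34% | 2.35, 64% |
| 0.5 | 1.000 | 1.86, 45% | 2.78, 79% |
| 0.7 | 0.775 | 2.39, 66% | 3.59, 94% |

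The range is 34% to 94%, against a nominal 5%.

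**3. Season and the between-arm test.** A rise common to both arms cancels in the difference. Simulation under the same assumptions (86 per arm, 4,000 runs per setting, shifts of 0 to 0.5 SD) gave significance at T2 in 4.5% to 5.6% of trials, that is, the nominal level.

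**4. Several visits.** This step applies only if significance at any of T1, T2 or T3 were accepted as success. For independent tests, the familywise error is 1 − 0.95³ = 14.3%. For correlated between-arm statistics it is 13.6% (r = 0.3), 12.5% (r = 0.5) and 10.9% (r = 0.7). The range is about 11% to 14%. T0 is not counted, because a baseline comparison cannot support a claim of effect.

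**The case against.** The strongest reply is that the article already points to the right comparison. The Design section says that the effect is read against control and that control is there to deal with season. The sample size is a two-group calculation. Within-arm tests fit the first secondary objective. The Discussion sentence is hedged and can be read as shorthand for an increase judged within that design. It also points to T2, and T3 is described as a check on persistence. The exact primary contrast and any multiplicity rule are often left to an analysis plan, and none is shown here.

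Most of this stands, and it rules out stronger readings that a reader might infer:

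- **That season threatens the trial's comparison as such.** It does not. The between-arm tests are protected from a shared rise, and the exposure is confined to the within-arm tests and the Discussion wording.
- **That success will be declared from a significant result at any visit.** The article states no such rule, so the 11% to 14% is conditional and is not the trial's error rate.
- **That the tests are uncorrected.** The article is silent on correction, and silence does not show that a rule is absent.
- **That retrospective registration leaves nothing to fix the deciding test.** The content of the registry record is not available here, so this cannot be known.

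The reply does not remove what is on the page. The one sentence that describes a supportive result omits the comparator, and the list of tests does not separate the contrast for which the trial was sized from tests that cannot isolate the programme.

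**Conclusion.** The point holds in a limited form. The Statistical analysis section does not rank its tests and the Discussion omits the control group from its description of a supportive result. Both fit poorly with the stated purpose of the control group and with the single between-arm test behind the 86 per arm.

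The size of the problem depends on how results are read. If an intervention-arm rise from T0 to T2 were taken as evidence, a seasonal shift alone would produce it in about 34% to 94% of trials. That figure rests on an assumed shared rise of 0.2 to 0.3 SD, a correlation of 0.3 to 0.7, and no allowance for clustering; the article gives none of these values. If the between-arm difference at T2 is what decides, a shared seasonal rise does no harm. This is a risk of misinterpretation that wording can remove. It does not show that the design fails.

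**What to change.** - In Statistical analysis, state that effectiveness is judged on one contrast: the between-arm difference in FV servings/day at T2, adjusted for baseline intake and allowing for clusters, at two-sided 0.05.
- Label the T1 and T3 comparisons and all within-arm changes as supportive.
- In the Discussion, reword the sentence so that the result of interest is an increase relative to the control group at the end of the programme.
- If an analysis plan exists, check that it names the same contrast.

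The change needs no new data or participants and agrees with the sample size calculation as a single two-group test. The small cost is that a result at T1 or T3, or a within-arm change, can no longer support the main claim alone.

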**Methods:**

Eligible classrooms within schools from Vitoria-Gasteiz (Basque Country, Spain) will be randomly assigned to the intervention (classrooms *n* = 4; children *n* = 86) or control (classrooms *n* = 4; children *n* = 86) group. The intervention group will receive 14 sessions of 60 min during an academic year (October to June). These sessions, designed by a multidisciplinary team, are based on TPB and are directed at modifying determinants of behavior (attitudes, subjective norms, perceived behavioral control and intention of consumption), and intake of FV itself. Both the process and the evolution of consumption and determinants of behavior will be evaluated (before, during, shortly after and a year after) using validated surveys, 7 day food records, 24 h reminders and questionnaires.

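### A negative result is called informative for redefining strategy with no condition on precision, yet with 4 v 4 classrooms a non-significant difference may well not exclude the trial's own target effect

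*Protocol article*

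**What the plan says.** The Discussion of the protocol article, and the Discussion paragraph of its abstract, state: "A negative result will be helpful in redefining new strategies in the framework of changing habits in the consumption of FV". Neither place defines a negative result or ties the statement to how precisely the effect is estimated.

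The other relevant statements are these:

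- **Target.** Sample size section: "In order to provide a power of 90% to detect an effect size (Cohen’s d) of at least 0.5 servings/day", for which "172 participants (86 in the intervention group and 86 in the control group) are required". With the dropout allowance, "the final sample size is increased by 20% to reach 206 children (8 classrooms with a minimum of 26 children per class").
- **Design.** Design section: "A cluster randomized controlled trial will be carried out over an academic year at school level", and "Classrooms from different schools and schools themselves will be the clusters of the study". The Methods paragraph of the abstract gives the allocation as ("classrooms *n* = 4; children *n* = 86) or control (classrooms *n* = 4; children *n* = 86) group".
- **Analysis.** The Statistical analysis section compares the groups at each time point by Student's t test or a rank test, with no classroom term. It closes with "IC of 95% and significance level of *p* < 0.05 will be assumed". The 95% interval is given no role in reading a null result.

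**The concern.** The only inferential threshold in the article is p < 0.05, so the natural reading of a negative result is a non-significant one, although the article does not say so. Non-significance can mean that the programme falls short of the target, or that the trial has too little information to tell. Only the first is a sound reason to rethink the strategy.

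The article names the effect it wants to detect but never compares a null result with it. Four classrooms per arm give limited information on a between-arm difference, so the second meaning is a real possibility. At stake is a programme that reached its target being read as one that did not.

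**Working it through.** **Inputs from the article.** 90% power, d = 0.5, 86 children per arm (Sample size); 4 classrooms per arm (abstract, Methods); p < 0.05 (Statistical analysis), taken as two-sided.

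**Assumptions.** The article gives no ICC, so 0 to 0.10 is shown. Equal classrooms of 86/4 = 21.5 analysed children, classroom as the only level of clustering, no gain from baseline adjustment. Effects are in SD units, so 0.5 SD equals 0.5 servings/day only if the SD is 1.

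**1. The plan's own figure.** A two-sided t test at 0.05 with d = 0.5 has power 0.8999 at 85 per arm and 0.9032 at 86. So 86 per arm, 172 in all, reproduces. It is the number for individually randomised children. The dropout step also reproduces: 172 × 1.2 = 206.4, given as 206; 8 × 26 = 208.

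**2. Allowing for classrooms.** DEFF = 1 + (21.5 − 1) × ICC. SE = √(2 × DEFF / 86). Degrees of freedom = 4 + 4 − 2 = 6, critical t = 2.447. Half-width = 2.447 × SE. Power is from the noncentral t with noncentrality 0.5 / SE.

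| ICC (assumed) | DEFF | SE (SD units) | 95% CI half-width | Power at d = 0.5 | Chance of non-significance at d = 0.5 |
|---|---|---|---|---|---|
| 0 | 1.00 | 0.152 | 0.37 | 78% | 22% |
| 0.02 | 1.41 | 0.181 | 0.44 | 64% | 36% |
| 0.05 | 2.025 | 0.217 | 0.53 | 49% | 51% |
| 0.10 | 3.05 | 0.266 | 0.65 | 35% | 65% |

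**3. When does a non-significant result exclude the target?** The upper limit is the estimate plus the half-width, so the target is excluded only if the estimate is below 0.5 minus the half-width:

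- ICC 0: below 0.50 − 0.37 = 0.13 SD. Estimates from 0.13 to 0.37 SD are non-significant and still compatible with the target.
- ICC 0.02: below 0.50 − 0.44 = 0.06 SD.
- ICC 0.05: below 0.50 − 0.53 = −0.03 SD. An observed difference of exactly zero does not exclude the target.
- ICC 0.10: below 0.50 − 0.65 = −0.15 SD.

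The half-width reaches 0.5 when DEFF = (0.5 / 2.447)² × 43 = 1.795, that is ICC = (1.795 − 1) / 20.5 = 0.039. These are half-widths at the expected SE; a realised interval on 6 df can be narrower or wider.

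**4. The child-level test as planned.** Its nominal half-width is t(170 df) × √(2/86) = 1.974 × 0.1525 = 0.301 SD, taken here as the same whatever the ICC. With the true SE from step 2, the chance of missing d = 0.5 is 10% at ICC 0, 18% at 0.05 and 23% at 0.10. But this interval appears to exclude 0.5 SD for any estimate below 0.50 − 0.30 = 0.20 SD, where a valid interval at ICC 0.05 needs an estimate below −0.03 SD. Its lower miss rate is bought with a type I error of about 17% at ICC 0.05 and 26% at ICC 0.10.

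**5. The unit.** If the target is 0.5 servings/day and the SD were, say, 1.5 servings/day (an assumption), d would be 0.5 / 1.5 = 0.33. The planned test would then miss the target about 42% of the time at ICC 0 and 44% at ICC 0.05.

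**The case against.** A reader might infer that the article commits to replacing the TPB programme after a non-significant result. It does not. Saying that a result will help in redefining strategies sets no decision rule and does not say that the programme or the theory has failed. The companion sentence on a positive result is itself hedged. This part of the objection stands in full.

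A reader might also infer that the trial cannot rule out its target at all. That is too strong. At an ICC of about 0.02 or less, a near-zero estimate would exclude 0.5 SD, and even at ICC 0.05 a slightly negative one would. The article gives no ICC, so the most that can be said is that a null result may well not exclude the target.

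The higher miss rates come from a classroom-level test that the article does not plan; under its own test they are 10% to 23%. This is correct, but it does not rescue the reading, because the planned interval is too narrow once the ICC exceeds 0.

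A null result on intake could still help redesign through the data on behavioural determinants and the SEM. That is a fair reading of the sentence, but it does not show whether the intake target was missed.

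Finally, the root defect is the lack of any clustering allowance in the sample size and analysis, and a condensed article may leave interpretation rules to the full plan. The first is true, yet restating the power would leave the two Discussion sentences unchanged. On the second, the article makes this interpretive statement itself, without qualification, and it can be judged as written.

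**Conclusion.** The point holds in a limited form. The article presents a negative result as informative without any condition on precision, while a non-significant result in this design may well be compatible with the effect it was sized to detect. A zone of results that are both non-significant and compatible with the target exists at every ICC examined; only its width depends on the ICC. Followed as written, the child-level interval could also make an inconclusive result look like evidence against the target.

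The size rests on the assumed ICC range, 86 analysed children per arm in equal classrooms, and no baseline adjustment. Adjustment for baseline intake would improve precision; additional clustering by school would reduce it. The change is worth making, but this is a matter of how a null result is read, not proof that the trial will mislead.

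**What to change.** Three linked changes are needed:

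1. **Statistical analysis:** take the between-arm difference in FV intake at T2, with its 95% CI, from an analysis that respects classrooms.
2. **Sample size:** state whether the 0.5 is in SD units or servings/day, and give the SD if it is the latter. Until this is settled, no upper limit can be compared with the target.
3. **Discussion and abstract:** say that a non-significant result counts against the programme reaching its target only if the upper limit of that CI lies below the target, and is otherwise inconclusive.

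No extra children or data are required. The cost is a change to the analysis method as well as to the wording, and some null results will have to be reported as inconclusive.
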